#### Statistical plan.

Analyses will address the relationships between neuropathy, neuropathic pain, quantitative sensory phenotype and microneurography measures of nociceptor excitability and axonal properties. Analyses will be prespecified, scripted for reproducibility and conducted using appropriate statistical software.

Continuous variables will be summarised using mean (standard deviation) or median (interquartile range) depending on distribution; categorical variables will be summarised using counts and percentages. Point estimators will be reported alongside their respective 95% confidence interval. All hypothesis tests will be two-tailed. Where multiple comparisons are performed, p-values will be adjusted using methods appropriate to the comparison (for example Bonferroni or false discovery rate), and this will be reported alongside unadjusted p-values.

The primary hypothesis is that participants with neuropathic pain will exhibit altered axonal properties and excitability compared to those without neuropathic pain. The primary outcome will therefore be a comparison of microneurography measures of axonal excitability and axonal properties between participants with and without neuropathic pain.

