#### Secondary analyses.

Secondary hypotheses explore relationships between somatosensory phenotype (QST clusters), genetic variants and nociceptor excitability signatures.

1. Somatosensory subgroup correspondence

- Compare microneurography variables across QST-defined phenotypic groups (sensory loss; mechanical hyperalgesia; thermal hyperalgesia) using non-parametric ANOVA (Kruskal–Wallis) or one-way ANOVA as appropriate.

- If omnibus tests are significant, perform post-hoc comparisons with correction for multiple testing.

2. Genetic variant effects

- Compare microneurography measures between participants who carry rare variants in ion channel genes (NaV, TRPA1) and those who do not, stratified by aetiology (diabetic versus non-diabetic).

- Use regression models to estimate the effect of genetic variants on fibre excitability, adjusting for confounders. If sample sizes for specific variants are small, present descriptive statistics and cautionary interpretation.

3. Microneurography association analyses

- Spearman rank-order correlations will evaluate associations between microneurography measures and clinical metrics: spontaneous pain intensity, evoked pain intensity, DN4/NPSI descriptor scores, and quality-of-life measures.

- A binomial regression model will examine the association between microneurography variables and membership of somatosensory subgroups.

Dimensionality reduction and clustering

Given the high dimensionality of clinical, genetic, microneurographic and biochemical data, we will use dimensionality reduction and unsupervised clustering to identify latent patient subgroups.

- Apply principal component analysis to standardised variables across the domains of interest (genetics, demographics, microneurography, biochemistry). Retain components that explain an adequate cumulative variance (e.g., eigenvalues >1).

- Apply k-means, centroid and hierarchical clustering on retained principal components. Determine optimal cluster number using multiple metrics (gap statistic, silhouette width, elbow method).

- After cluster assignment, compare original variables across clusters using omnibus tests with post-hoc comparisons to characterise cluster profiles.

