#### Sample size justification.

Sample size calculations are based on power to identify differences in QST cluster frequencies and to support clustering and multivariate analyses.

- Using pilot quantitative sensory testing data from DOLORisk, expected cluster frequencies for diabetic distal symmetrical polyneuropathy are 53.9% (sensory loss), 25.0% (mechanical hyperalgesia) and 15.8% (thermal hyperalgesia). For non-diabetic neuropathies the corresponding frequencies are 49.7%, 21.2% and 14.5%.

- For moderate effects (Cohen’s d ~ 0.5) in the quantitative sensory testing cluster analyses, a total of 130 diabetic and 148 non-diabetic participants provides approximately 80% power at α = 0.05.

- For k-means and hierarchical clustering applied after principal component analysis, a conservative estimate requiring 2^8 = 256 participants was used to ensure adequate representation across variable permutations.

- A multivariate regression model with age, sex, diabetes status, neuropathy severity, and medication use will require 8 degrees of freedom to represent all its variables (assuming a categorical variable coding for 4 categories of medication). Allowing for at least 15 event per variable (EPV) we will require a sample size of at least 120 participants for model development. As described above, variable selection and filtering based on multicollinearity will likely increase the EPV.

- Taking these calculations together (and accounting for anticipated success rates in microneurography recordings: minimum 60% for diabetic participants and 80% for non-diabetic participants), the recruitment target is 272 participants (124 diabetic and 148 non-diabetic).

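### P-values for variables that were used to form the clusters have no valid null distribution, so cluster profiles on those variables should be reported descriptively

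*Protocol article*

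**What the plan says.** The relevant text is in the protocol article, Secondary analyses, under the sub-heading on dimensionality reduction and clustering. The aim is stated first: "we will use dimensionality reduction and unsupervised clustering to identify latent patient subgroups". The steps then run in a fixed order.

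1. Inputs: "Apply principal component analysis to standardised variables across the domains of interest (genetics, demographics, microneurography, biochemistry").
2. Grouping: "Apply k-means, centroid and hierarchical clustering on retained principal components".
3. Number of groups: "Determine optimal cluster number using multiple metrics (gap statistic, silhouette width, elbow method").
4. Testing: "After cluster assignment, compare original variables across clusters using omnibus tests with post-hoc comparisons to characterise cluster profiles".

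The original variables in step 4 are naturally read as the inputs of step 1. The article names no sample split, held-out set, selective-inference method or permutation reference for step 4, and it does not restrict the step to description. The only general protection is in the Statistical plan section: multiplicity adjustment, with Bonferroni and false discovery rate as examples.

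**The concern.** An omnibus test such as one-way ANOVA or Kruskal–Wallis takes its reference distribution from group labels that are unrelated to the variable under the null hypothesis. Here the labels are computed from the variable. A clustering algorithm looks for a partition with small within-group spread on the components, and the components are linear combinations of the variables. The variables will therefore tend to differ between groups whether the population holds distinct subgroups or is one continuous cloud. Adjusting for the number of tests does not help, because the fault lies in each single test.

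At stake is how the subgroups are read. The abstract presents clustering as a route to subgroups grounded in mechanism, and the Sample size justification section uses clustering as one of its drivers (256 participants). A table of very small omnibus and post-hoc p-values would look like evidence that the subgroups differ on nociceptor measures, when such a table is expected from the procedure itself.

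**Working it through.** The article states no error rate for this step, so there is no figure of its own to reproduce. The check is to run the planned sequence on data that contain no subgroups.

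**Inputs from the article**
- Participants with microneurography data, from the recruitment target and recording success rates in Sample size justification: 124 × 0.60 + 148 × 0.80 = 74.4 + 118.4 = 192.8, about 193. The full target is 124 + 148 = 272.
- Nominal level 0.05. The article gives it for the QST cluster power statement ("provides approximately 80% power at α = 0.05"); I assume the same level for the post-cluster tests.
- Sequence: standardise, principal components, keep eigenvalues above 1 (the article's example), cluster, then test each original variable across clusters.

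**Assumptions, not in the article**
- 8, 20 or 40 Gaussian variables; pairwise correlation 0 or 0.3; 2, 3 or 4 clusters imposed.

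**Result 1: share of original variables with p<0.05 when no subgroups exist (nominal 5%)**

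First set of runs: 193 participants, independent variables, k-means, Kruskal–Wallis, 100 datasets per setting:

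| Variables | 2 clusters | 3 clusters |
|---|---|---|
| 8 | 75% | 93% |
| 20 | 59% | 78% |
| 40 | 48% | 62% |

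Separate set of runs, one-way ANOVA, 150 to 300 datasets per setting (200 for Ward):

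| Setting | 2 clusters | 3 clusters | 4 clusters |
|---|---|---|---|
| n=193, 8 variables, correlation 0 | 76% | 93% | 99% |
| n=193, 20 variables, correlation 0 | 61% | 79% | 87% |
| n=193, 8 or 20 variables, correlation 0.3 | 100% | 100% | 100% |
| n=272, 8 variables, correlation 0 | 79% | 95% | 99% |
| n=272, 20 variables, correlation 0 | 65% | 84% | 92% |
| n=272, 20 variables, correlation 0, Ward clustering | 55% | 76% | 87% |

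Kruskal–Wallis agreed with ANOVA to within about 1.5 percentage points.

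**Result 2: does multiplicity adjustment help?** The Bonferroni thresholds are 0.05/8 = 0.00625, 0.05/20 = 0.0025 and 0.05/40 = 0.00125. At least one variable passed in 100% of datasets in every setting.

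**Result 3: is circularity the cause?** In the second set of runs, five further independent noise variables per dataset were kept out of the clustering and tested in the same way. They rejected in 3.5% to 6.5% of tests. With 150 datasets × 5 = 750 tests, the simulation standard error is √(0.05 × 0.95 / 750) = 0.008, so both ends of that range lie within two standard errors of 5%. The tests behave properly when the variable played no part in forming the groups.

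**Result 4: would the planned choice of cluster number stop this?** The gap statistic was applied to noise of the same kind (n=272; 8 or 20 variables; correlation 0 or 0.3; 25 datasets each; 20 reference sets). It chose one cluster in 4 × 25 = 100 of 100 datasets. Silhouette width is not defined for a single cluster, and the elbow method does not test for one; these two points follow from the definitions and were not simulated.

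**The case against.** The strongest reply is that the simulation imposes two or more clusters, whereas the plan chooses the number. The gap statistic is listed first among its metrics and returned one cluster in every noise dataset. This stands. The percentages are conditional on accepting at least two clusters and are not error rates of the whole plan. A reader might infer that the plan would declare subgroups in pure noise; the documents do not support that. The safeguard is partial, however: it is one of three metrics, at least one of the others cannot point to a single cluster, and the article gives no rule for disagreement. Such a rule could sit in the analysis plan, so its absence is not the finding. Nor would it rescue the tests: where real clusters exist, the p-values for the clustering variables still lack a valid reference distribution.

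A second reply is that the stated purpose is to characterise profiles, not to confirm subgroups, and that the step is secondary. This also stands. The comparison of participants with and without neuropathic pain, and the numbered secondary analyses on QST groups, genetic variants and clinical associations, do not use these clusters. But omnibus and post-hoc tests are inferential tools; if description is all that is wanted, the p-values add nothing.

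A reader might also infer that keeping components with eigenvalues above 1 makes the problem worse. It does not. With 193 participants, 20 independent variables and 2 clusters, the share rejected was 0.60 with 2 components, 0.58 under the eigenvalue rule and 0.59 with all 20; 8 and 40 variables likewise showed no material effect. The article offers that rule only as an example.

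**Conclusion.** The concern holds in a limited form. As written, the article prescribes significance tests of variables across groups built from those same variables. Conditional on two or more clusters being accepted, these p-values cannot be interpreted at their nominal level, and the planned multiplicity adjustment does not change that.

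The size rests on assumed inputs. For 193 participants, 8 to 40 independent Gaussian variables and 2 or 3 k-means clusters, about 48% to 93% of pure-noise variables reach p<0.05. With correlation 0.3 (8 or 20 variables) all of them do. Every setting tried was far above 5%. The exact figure will depend on the number of variables, their correlation and the number of clusters, none of which the article gives; the direction does not depend on them. This is worth correcting before the clustering analysis is run, but it does not touch the primary result.

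**What to change.** Change the wording of the final clustering step in three ways.

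1. For every variable that entered the principal component analysis, describe the cluster profile with standardised means or medians and give no p-values.
2. Keep hypothesis tests for variables held out of that analysis, for example pain status, pain intensity, QST phenotype and quality of life. This needs an explicit list of inputs: the lead-in sentence mentions clinical data, while the list of domains for the component analysis does not. A significant held-out test shows association with the cluster label; it does not by itself prove that distinct subgroups exist, because a held-out variable may simply correlate with an input.
3. State that no subgroups will be claimed if the gap statistic selects one cluster.

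A bootstrap check of cluster stability would be a useful addition but is not needed to remove the error.

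The cost is a few lines of analysis-plan text and fewer p-values to report. No new data are needed, and recruitment and data collection are scheduled to run until September 2029, so there is time to make the change.

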#### Sample size justification.

Sample size calculations are based on power to identify differences in QST cluster frequencies and to support clustering and multivariate analyses.

- Using pilot quantitative sensory testing data from DOLORisk, expected cluster frequencies for diabetic distal symmetrical polyneuropathy are 53.9% (sensory loss), 25.0% (mechanical hyperalgesia) and 15.8% (thermal hyperalgesia). For non-diabetic neuropathies the corresponding frequencies are 49.7%, 21.2% and 14.5%.

- For moderate effects (Cohen’s d ~ 0.5) in the quantitative sensory testing cluster analyses, a total of 130 diabetic and 148 non-diabetic participants provides approximately 80% power at α = 0.05.

- For k-means and hierarchical clustering applied after principal component analysis, a conservative estimate requiring 2^8 = 256 participants was used to ensure adequate representation across variable permutations.

- A multivariate regression model with age, sex, diabetes status, neuropathy severity, and medication use will require 8 degrees of freedom to represent all its variables (assuming a categorical variable coding for 4 categories of medication). Allowing for at least 15 event per variable (EPV) we will require a sample size of at least 120 participants for model development. As described above, variable selection and filtering based on multicollinearity will likely increase the EPV.

- Taking these calculations together (and accounting for anticipated success rates in microneurography recordings: minimum 60% for diabetic participants and 80% for non-diabetic participants), the recruitment target is 272 participants (124 diabetic and 148 non-diabetic).

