#### Quantitative sensory testing.

Quantitative sensory testing is a psychophysical technique used to assess sensory perception in response to defined stimuli. It provides a quantitative measure of sensory function and generates a sensory profile that captures both loss and gain of function across multiple sensory modalities. Quantitative sensory testing will be performed according to a modified version [42] of the German Research Network on Neuropathic Pain (DFNS) protocol [20,57]. In this study population, most participants are expected to experience bilateral symptoms; therefore, testing will be performed unilaterally on the dorsum of the foot and/or hand.

Quantitative sensory testing data will be entered into the Equista software package (version 1.2.2., CASQUAR GmbH), developed by the German Research Network on Neuropathic Pain. Equista converts raw data into z-scores, normalising results for age, sex, and the body region tested [58]. A z-score of zero represents the population mean, while scores greater than +2 or less than –2 standard deviations indicate gain or loss of function, respectively.

Participants will be stratified into somatosensory phenotype groups based on their quantitative sensory testing results. Two complementary approaches will be used:

Cluster analysis – An unbiased algorithm identifies three distinct phenotypic groups: sensory loss, mechanical hyperalgesia, and thermal hyperalgesia. Individuals will be assigned deterministically to one of these groups [13,19].Irritable versus non-irritable phenotype – Participants will be classified as having an irritable phenotype when detection thresholds are normal but there is evidence of sensory gain (mechanical or thermal hyperalgesia), or a non-irritable phenotype when there is either sensory loss or no evidence of sensory gain [59].

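### The stated 80% power for the QST cluster analyses holds only if three clusters are collapsed to two and everyone yields data; it does not hold for the planned three-cluster test, and the primary comparison has no power statement

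*Protocol article*

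**What the plan says.** The Sample size justification opens: "Sample size calculations are based on power to identify differences in QST cluster frequencies" (it adds support for clustering and multivariate analyses). It gives pilot cluster shares of 53.9%, 25.0% and 15.8% in diabetic neuropathy and 49.7%, 21.2% and 14.5% in non-diabetic neuropathy, in the order sensory loss, mechanical hyperalgesia, thermal hyperalgesia. With α set at 0.05 and a Cohen's d of roughly 0.5, its claim for the cluster analyses is: "a total of 130 diabetic and 148 non-diabetic participants provides approximately 80% power". It names neither the test nor the groups contrasted.

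The cluster test itself stands under Secondary analyses: microneurography variables are compared across the three clusters by Kruskal-Wallis or one-way ANOVA, with corrected post-hoc comparisons if the omnibus test is significant. The Statistical plan adds: "All hypothesis tests will be two-tailed". On cluster membership, the Quantitative sensory testing section says: "Individuals will be assigned deterministically to one of these groups".

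The primary question is a different one: "The primary hypothesis is that participants with neuropathic pain will exhibit altered axonal properties and excitability compared to those without neuropathic pain". The remaining sizing bullets are a 2^8 = 256 rule for clustering and an events-per-variable rule (8 × 15 = 120) for the regression model. The recruitment target is 272 (124 diabetic, 148 non-diabetic), with minimum microneurography success of 60% and 80%.

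**The concern.** This is the only power figure in the protocol. Cohen's d is a standardised difference between two means, whereas the plan has three clusters of clearly unequal size and says the calculation concerns frequencies. A d of 0.5 with about 130 participants gives 80% in an ordinary two-group comparison, so the figure may have been carried over to a three-group analysis that it does not describe. The figure also counts all participants, although the variables compared across clusters exist only where a recording succeeds.

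At stake is how results are read. A null cluster comparison could be taken as coming from a test with 80% power when the planned test has much less. For the primary comparison, the reader is not told what size of difference the study can detect.

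**Working it through.** **Inputs.** d = 0.5 with SD 1, α = 0.05, N = 130 and 148, cluster shares, success rates and recruitment target: all from the Sample size justification. Two-sided testing: Statistical plan. Three-group test: Secondary analyses.

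**Cluster sizes** (share × N, fractions kept):
- Diabetic, 130: 70.1 / 32.5 / 20.5, remainder 6.9.
- Non-diabetic, 148: 73.6 / 31.4 / 21.5, remainder 21.6.
- The shares sum to 53.9 + 25.0 + 15.8 = 94.7% and 49.7 + 21.2 + 14.5 = 85.4%.

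**Evaluable numbers** at the minimum success rates: 0.60 × 124 = 74.4 and 0.80 × 148 = 118.4, total 192.8. The target of 124 diabetic participants is itself below the 130 in the power bullet.

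**Formulas.**
- Two groups: non-centrality δ = d·√(n₁n₂/(n₁+n₂)); power = P(|T| > t₀.₉₇₅), T noncentral t with n₁+n₂−2 df.
- Three-group omnibus, one cluster k shifted by 0.5 SD: λ = 0.25·n_k(M−n_k)/M, where M is the number in the three clusters; power = P(F > F₀.₉₅), F noncentral with 2 and M−3 df.

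**Step 1: reproduce the plan's figure.** Two equal halves: δ = 0.5·√(65·65/130) = 2.85, power 80.8% for 130; 85.6% for 148. Sensory loss against both hyperalgesia clusters (70.1 v 53.0): δ = 2.75, power 77.8% (78.4% by the normal approximation). For 148 (73.6 v 52.8): δ = 2.77, power 78.6% (79.2%). Sensory loss against everyone else: 80.5% and 85.6%. So about 80% is recovered by a two-group contrast.

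**Step 2: the planned test.** Examples at N = 130: for sensory loss v mechanical, δ = 0.5·√(70.1·32.5/102.6) = 2.36, power 64.6%; for the omnibus with thermal shifted, λ = 0.25·20.5·102.6/123.1 = 4.28, power 43.1%.

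| Power (%) at d = 0.5 | Diabetic 130 | Non-diabetic 148 | Diabetic 74.4 | Non-diabetic 118.4 |
|---|---|---|---|---|
| Loss v hyperalgesia pooled | 77.8 | 78.6 | 53.6 | 69.0 |
| Loss v all others | 80.5 | 85.6 | 56.4 | 77.0 |
| Omnibus, loss shifted | 67.9 | 68.8 | 42.7 | 58.1 |
| Omnibus, mechanical shifted | 57.1 | 56.5 | 34.8 | 46.7 |
| Omnibus, thermal shifted | 43.1 | 44.7 | 25.8 | 36.5 |
| Loss v mechanical | 64.6 | 64.2 | 41.8 | 54.5 |
| Loss v thermal | 50.4 | 52.3 | 31.5 | 43.6 |
| Mechanical v thermal | 41.3 | 41.7 | 25.4 | 34.4 |

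With Bonferroni for three pairs (α = 0.05/3), the pairs at 130 and 148 fall to 25-47%.

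**Step 3: the primary comparison.** The plan gives nothing to reproduce. As an illustration, suppose all 193 evaluable participants enter. By the normal approximation, the detectable d at 80% power is (1.960 + 0.842)·√(1/96 + 1/97) = 0.40; the exact t value is 0.41. At a 1:2 split it is 0.43. With Bonferroni for six measures the values are 0.51 and 0.54. The split and the number of measures are assumptions; the protocol's list of measures is introduced as examples, and it also allows a false discovery rate method.

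**The case against.** The best defence is that the bullet names no test, so it cannot be held to the three-group one. Two-group readings have support elsewhere: the protocol plans a binomial regression for subgroup membership and defines an irritable versus non-irritable phenotype. Sensory loss against pooled hyperalgesia, at the plan's own unequal shares, gives close to 80% in both strata and would explain why the non-diabetic number is the larger. This stands. A reader might infer that the 80% cannot be reproduced, that it needs two equal groups, or that no cluster contrast reaches it; Step 1 shows that none of these is so. What the defence does not supply is a statement that this contrast was the one powered, or data from every participant.

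Three other stronger readings also fail:
- Taking the bullet literally as diabetic versus non-diabetic cluster frequencies gives about 6% power, but only if the remainders are dropped and the shares rescaled to 100%. Keeping the remainder as a further category gives 56%. The low figure is a product of that choice.
- The missing 5.3% and 14.6% might be taken as a group without abnormal profile. The documents do not say what they are; incomplete pilot testing is equally possible.
- The lack of a power statement does not show that the primary comparison is underpowered. At d = 0.5 with 193 evaluable and an even split, unadjusted power is about 93%.

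It is also fair to say that the 120-participant rule addresses the covariate-adjusted pain model. It is a sizing rule, however, and not a statement of power. Finally, the cluster comparison is secondary and confidence intervals will be reported, which limits the damage.

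**Conclusion.** The point holds in this form. The 80% is approximately correct for a two-group collapse with complete data, a contrast that the protocol does not state. It is not a property of the three-cluster comparison that the protocol plans: 43-68% (diabetic) and 45-69% (non-diabetic) for the omnibus test, and 41-65% for single pairs before correction. At the minimum recording rates, none of the contrasts in the table reaches 80% within either stratum: omnibus 26-43% and 37-58%, pairs 25-42% and 34-55%, two-group collapse 54-56% and 69-77%. The effect measure does not match the stated basis in cluster frequencies, and the primary comparison has neither power nor a detectable difference.

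The percentages assume d = 0.5 as the shift of one cluster or the difference within a pair, normal data with equal variances, the pilot shares holding in this study and among those with recordings, and success at the stated minima. Higher success rates would move the evaluable figures towards those for full recruitment, which still fall short for the planned test.

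**What to change.** 1. Rewrite the power bullet so that it names the contrast and the outcome, and replace the reference to cluster frequencies or the use of Cohen's d so that the two agree.
2. Give the power for the planned three-cluster test and its corrected pairs at the stated shares, for recruited and for evaluable numbers. If a two-group contrast was intended, say so and list it among the planned analyses.
3. Add a detectable difference for pain versus no pain, labelled as resting on assumptions: about 193 evaluable, all entering the comparison, d = 0.41 at an even split and 0.43 at 1:2 (0.51 and 0.54 with Bonferroni for six measures).
4. Explain why the shares sum to 94.7% and 85.4% when each individual is to be placed in one of three groups, and state how the remainder is handled, without presuming what it is.

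The cost is in wording only: the stated power becomes less favourable, and no extra participants are required.

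### The clustering figure of 2^8 = 256 lacks the property claimed for it: it averages one participant per combination and does not describe clustering on component scores

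*Protocol article*

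**What the plan says.** The Sample size justification gives several calculations that are taken together to reach the target: "the recruitment target is 272 participants (124 diabetic and 148 non-diabetic". One of them concerns the cluster analyses. It opens "For k-means and hierarchical clustering applied after principal component analysis" and continues "a conservative estimate requiring 2^8 = 256 participants was used to ensure adequate representation across variable permutations". The sentence does not name eight variables, say that they have two levels, or give a minimum number per combination.

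The method being sized is under Secondary analyses, in the part on dimensionality reduction and clustering: "Apply k-means, centroid and hierarchical clustering on retained principal components". The number of components is left to the data: "Retain components that explain an adequate cumulative variance (e.g., eigenvalues >1".

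**The concern.** The sentence makes two claims about 256 beyond its use as a requirement: that it is conservative, and that it guarantees coverage of the combinations of variables. Neither fits a sample size that merely equals the number of combinations. The count also belongs to cross-classified binary variables, whereas the plan clusters continuous scores.

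What is at stake is how the subgroup results will be read. The abstract presents clustering as the route to mechanistically informed patient subgroups. A published statement that the analysis was conservatively sized lends those subgroups, or their absence, a support that the document has not established. The primary comparison of participants with and without neuropathic pain does not depend on it.

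**Working it through.** **Inputs.** From the Sample size justification: 2^8 = 256; recruitment of 124 diabetic and 148 non-diabetic participants; recording success of "minimum 60% for diabetic participants and 80% for non-diabetic participants". The probabilities of the combinations are not given. I assume eight independent two-level variables, first with both levels equally common, then with prevalences from 0.4 down to 0.1.

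**1. The plan's figure.** 2^8 = 256 reproduces exactly.

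**2. Mean per combination.** N / 2^8 = 256 / 256 = 1.0.

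**3. Expected share empty, equal probabilities.** (1 − 1/256)^N at N = 256 is (255/256)^256 = 0.367, or about 94 of the 256 combinations. In 20,000 simulated samples the middle 95% ran from 84 to 104.

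**4. Expected share with exactly one participant.** N × (1/256) × (255/256)^(N−1) = (255/256)^255 = 0.369. The share with two or more is 1 − 0.367 − 0.369 = 0.264.

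**5. Why 36.7% is a floor.** The function (1 − q)^N is convex in q, and the 256 probabilities average 1/256 whatever their values. Unequal probabilities can therefore only raise the expected share empty. With a common prevalence p, that share is the sum over j = 0 to 8 of C(8, j) × [1 − p^j (1 − p)^(8−j)]^256, divided by 256:

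| Prevalence of each variable (assumed) | Expected share empty at N = 256 |
|---|---|
| 0.5 | 37% |
| 0.4 | 42% |
| 0.3 | 55% |
| 0.2 | 70% |
| 0.1 | 85% |

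**6. At the plan's other counts, equal probabilities.** At the target of 272 the share empty is (255/256)^272 = 34.5%. At the stated minimum success rates, usable recordings number 124 × 0.60 + 148 × 0.80 = 74.4 + 118.4 = 192.8, about 193. That gives 193 / 256 = 0.75 per combination and 47% empty. The point does not turn on these counts, because the claimed property already fails at 256.

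**7. Match to the method.** Principal-component scores are continuous, so they do not form 2^8 combinations. Nothing in Secondary analyses fixes the number of retained components at eight. The rule thus fails on its own terms and also counts something that the planned analysis does not use.

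**The case against.** The strongest reply is that empty combinations do no harm here. K-means and hierarchical clustering on component scores do not need every combination filled, so the 37% measures no loss in any planned result. This stands in full.

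An illustrative simulation supports it. I assumed eight dimensions, three equidistant clusters with shares 57/26/17%, k-means given the correct number of clusters, and 40 replicates per setting. The adjusted Rand index (1 = perfect recovery) over repeated runs was:

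| Separation | N = 256 | N = 1,280 | True centres and shares known |
|---|---|---|---|
| 2 SD | 0.24–0.25 | 0.30–0.31 | about 0.45 |
| 3 SD | 0.62–0.63 | 0.63–0.65 | about 0.72 |
| 4 SD | 0.85–0.87 | 0.87 | about 0.90 |

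Five times the sample adds at most about 0.02 at 3 to 4 SD. At 2 SD recovery is poor at either size. Overlap between clusters limits recovery more than the sample size does.

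A reader might therefore infer two things that the documents do not support. One is that 256 is too few for clustering; neither the occupancy count nor the simulation shows this. The other is that a fixed separation, such as 3 SD, marks the limit of reliable recovery. The documents give no separation, number of clusters or number of dimensions, and the result moves with the assumed geometry: with the centres on a line, the 3 SD figures become 0.68 at 256 and 0.73 at 1,280.

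It can also be said that eight binary variables is an inference, and that a condensed article may leave the derivation to a fuller document. The inference is fair to flag, but the text offers no other reading of 2^8 alongside its reference to permutations. The point concerns what the article asserts, not what it leaves out.

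**Conclusion.** The point holds as a fault in the stated justification. Read as eight two-level variables, 256 participants give a mean of one per combination, with at least 36.7% expected empty. The mean follows directly from the plan's own figure. The 36.7% assumes equally likely combinations, which is the most favourable case. The words conservative and ensure are therefore unsupported, and the rule does not correspond to clustering on a data-driven number of component scores.

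The consequence is limited. The analysis is secondary, the primary comparison is unaffected, and the adequacy of 256 for clustering is neither shown by the article nor disproved here.

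**What to change.** In the Sample size justification, delete the adjective conservative and the clause "to ensure adequate representation across variable permutations". Say instead, in substance: 2^8 = 256 is a rule of thumb that corresponds to about one participant per combination of eight two-level variables, and it does not establish that clustering on component scores is adequately sized.

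Then do one of the following:

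- Present the clustering as exploratory, with no sample-size guarantee.
- Support it with a short simulation of cluster recovery at the expected evaluable number (about 193 at the stated minimum success rates, if microneurography data are required), over a stated range of separations, cluster numbers and dimensions.

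Word the subgroup conclusions to match whichever is chosen. Do not fix a single separation threshold, and do not report the share of empty combinations as a loss in clustering performance.

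The cost is one reworded paragraph and, under the second option, a short simulation. Recruitment and study procedures do not change. The price is that a reassuring statement about sample size is withdrawn.
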